### Intervention

Subjects in the intervention group participate in a 6-month multifactorial, tailored nutritional counselling consisting of two individual sessions with a personal nutrition plan described below and three group counselling sessions in smaller groups with 15–20 individuals. Combining individual and group counselling allows participants to meet their personal needs, set individual goals and receive peer support. The sessions are held monthly at participants’ workplaces or at the university. Table 3 presents the themes and content of the sessions in chronological order. The principles of nutrition counselling are based on the Finnish Nutrition recommendations (Finnish National Nutrition Council and Finnish Institute for Health and Welfare, 2024). We will advise the participants on the following while taking into consideration their individual needs:
1.Vegetables, fruit and berries: at least 500–800 g daily in total2.Whole grain products: at least 90 g daily, meaning, for example, three slices of bread, one portion of oatmeal and one decilitre of cooked barley groats3.Unsweetened, fat-free or low-fat dairy products: 350–500 mL daily4.Non-tropical vegetable oils and vegetable-oil-based margarine: at least 25 g daily, avoiding butter and tropical oils5.Fish: 300–450 g weekly, including at least 200 g of fatty fish6.Pulses and legumes: 50–100 g (cooked), to replace meat and poultry, at least partly7.Red meat: maximum of 350 g (cooked) weekly and avoidance of processed meat8.Maximum of one egg daily9.Water is the main drink10.Added sugar as little as possible (maximum of 10% of energy intake)

**Table 3. table3-02601060251332358:** Content of the nutrition counselling sessions.

	Theoretical framework	Content	Session and home assignments
**1^st^ individual session:** Personal nutrition plan	Goal attainment scaling (GAS; Kiresuk and Sherman, 1968)	Evaluation and feedback on the participants’ diet	Personal goal setting
**1^st^ group session:** Everyday life and meal frequency	Psychoeducation	Introduction theme: Diet and depression Theme: Importance of regular meal frequency	Daily factors associated with own mental well-being Home: Test of dietary habits
**2^nd^ group session:** Good food, better mood	Peer support (Lim et al., 2021) Mindful eating (Nelson, 2017)	Notes of dietary habits: pros and cons Theme: Health-promoting diet, topic requests of the participants Mindful eating activity	Home: Adding a mind-friendly food item to one's diet Home: Daily life lists of futilities, successes and reasons for gratitude
**2^nd^ individual session:** Goal attainment and further plan	GAS (Kiresuk and Sherman, 1968) Motivational interviewing (Miller, 1996)	Discussion about goal attainment, motivation and challenges	Evaluation of goal attainment
**3^rd^ group session:** Hope for the future	Psychology of long-term lifestyle changes (Teixeira et al., 2015)	Theme: Successful eating regulation skills	Successes during the intervention

#### Individual counselling

The main contribution of the intervention is the individually tailored nutrition counselling provided to each participant by the same research nutritionist. The focus is on the personal goal towards the adoption of the recommended diet by participants through personalized goal setting. The first individual counselling session lasts 1–1.5 h. During the first session (Table 3), the nutritionist evaluates the participant's background factors, dietary habits, nutrient intake and eating behaviour. The participant sets adequate goals and means to achieve them with the nutritionist. The framework is the GAS method (Kiresuk and Sherman, 1968). Goals and means will be written in the personal nutrition plan. During the second individual meeting (1 h), the achievement of the goals will be assessed using the GAS method (Kiresuk and Sherman, 1968) and potential challenges and solutions will be discussed by applying the principles of motivational interviewing (Miller, 1996).

#### Group counselling

Participants will attend three nutrition-focused group counselling sessions, each lasting 1–1.5 h (Table 3). Each session will have its own theme and assignments for the meetings and homework. Some tasks are modified versions of those used in the StopDia diabetes prevention study (Pihlajamäki et al., 2019). Participants will receive a workbook containing the assignments and informational material. The first group session theme addresses daily routines and benefits of a regular meal frequency and includes a brief introduction to the background of the Mind Nutrition study. Participants can also request personally meaningful topics that will be covered in subsequent meetings.

The second group session focuses on the principles of a health-promoting diet. Participants share their health-promoting and unfavourable habits and receive peer support, fostering a sense of connection, sharing novel ideas and empowerment from others. The theme will be covered in a healthy diet lecture, considering the requests of the participants. The first home assignment – adding a ‘mind-friendly food item’ – means testing a new food related to a lower risk of depression, such as fish or vegetables high in folate. The purpose of the ‘daily life lists’ assignment is to scrutinize daily routines and time management as factors influencing eating habits.

The last group session directs attention towards the future. Participants will assess what they have learned and how they have succeeded during the intervention. The final theme addresses eating patterns and behavioural skills.

### Statistical analyses

The results will be analysed using the IBM SPSS Statistics program and the STATA program. A statistician unrelated to the study will perform the statistical analyses. The analyses will utilize the intention-to-treat principle (Soares and Carneiro, 2002).

The normality of variables will be examined graphically and using the Shapiro–Wilk test. For the descriptive statistics, comparisons between groups will be analysed using the independent samples *t*-test for continuous, normally distributed variables, the chi-squared test for categorical variables and the Mann–Whitney *U* test for non-normally distributed variables. The difference between groups in the change in depressive symptoms, quality of life and diet quality is continuous variables and will be analysed with repeated analysis of variance. The difference between groups in the change in work ability and sick leave days related to depressive symptoms is ordinal variables and will be analysed with mixed-effect models for ordinal data. The main outcomes will be examined first overall and then stratified by gender to assess potential gender differences in intervention effectiveness.

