#### Sample size calculation

We calculated the sample size based on the expected change in depressive symptoms, measured with the CES-D scale (Radloff, 1977). We expect depressive symptoms to decrease in the intervention group from 14 to 9.9 points (Katsuta et al., 2021; Konttinen et al., 2010; Mondal et al., 2022) and assume that depressive symptoms will not change in the control group. The calculation is based on an estimated power of 0.8 with an expected dropout rate of 25%. The calculated sample size was 125, meaning 62 or 63 participants per group (ß = 0.2, a 0.05).

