#### Primary and secondary outcomes

Table 1 presents the primary and secondary outcomes. The outcomes will be assessed utilizing the electronic survey at baseline and after 6 months.

**Table 1. table1-02601060251332358:** Primary and secondary outcomes.

Primary outcome variables	Measurement
Depressive symptoms	CES-D (Radloff, 1977)
Work ability	Current work ability compared with the lifetime best (Tuomi et al., 2007) Three-level work ability indicator (Gould et al., 2015)
Secondary outcome variables	Measurement
Sick leave days related to depressive symptoms	Structured question about sick leave days during the past 6 months
Quality of life	WHO8-EUROHIS (WHO, Power, 2003)
Dietary habits	Food Frequency Questionnaire (Männistö et al., 1996) Healthy Diet Index (HDI; Lindström et al., 2021) Three-day food records Three Factor Eating Questionnaire – 18 (TFEQ-18; Karlsson et al., 2000)
Intervention adherence	Goal Attainment Scaling (GAS; Kiresuk and Sherman, 1968) Level of participation
Intervention acceptability	The Theoretical Framework for Acceptability (TFA; Sekhon et al., 2022)

CES-D: Center for Epidemiological Studies – Depression; TFEQ-18: Three Factor Eating Questionnaire – 18; WHO: World Health Organization.

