##### Primary outcome: Change in depressive symptoms

The primary outcome is the change in depressive symptoms measured with the CES-D scale (Radloff, 1977). This scale is commonly used to assess depressive symptoms in the general population. Its 20 items enquire about various symptoms of depression experienced over the past week, such as feelings of sadness, loss of interest and sleep disturbances. Each item is scored on a scale from 0 to 3, indicating the frequency of experiencing that symptom (0 = Rarely or none of the time, 1 = Some or a little of the time, 2 = Occasionally or a moderate amount of time, 3 = Most or all the time). Points from questions 4, 8, 12 and 16 are reverse-scored. The total CES-D score is the sum of the responses to all items, between 0 and 60, with a higher score reflecting more severe depressive symptoms. Typically, a cut-off score of 16 or more points indicates significant depressive symptoms.

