One limitation is the lack of blinding of the participants and study staff in this type of intervention. However, this is unlikely to cause bias for the investigators, as the data come from questionnaires completed by the participants and because the intervention provider will not analyse the data. The second limitation concerns the issues related to the questionnaires, such as temporal variability and treatment expectations that can influence the responses. However, we will use validated questionnaires to minimize these issues. The third potential limitation is that subjects randomized to the control group might withdraw from the study. We try to reduce the risk by offering them one nutrition counselling session, feedback on their food records and a personal nutrition plan after the intervention. The fourth possible limitation is that the participants in both groups may modify their eating habits because they are aware of being observed, the phenomenon known as the Hawthorne effect (Sedgwick and Greenwood, 2015). Moreover, participants in the intervention and control groups may have different treatment expectancies that can influence their behavioural and self-reported outcomes.

This study will provide novel evidence of the effectiveness of nutrition counselling on depressive symptoms among mental health and substance abuse professionals. Based on the acquired knowledge, prevention programmes can be implemented for the targeted population to sustain their mental health, quality of life and work ability.

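### The article promises intention-to-treat, but the repeated-measures ANOVA it names for CES-D, quality of life and diet quality can use only participants with both scores, at a planned 25% dropout

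*Protocol article*

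**What the plan says.** The protocol article, Statistical analyses, sets the principle without qualification: "The analyses will utilize the intention-to-treat principle". The next paragraph fixes the methods. The between-group difference in change in depressive symptoms, quality of life and diet quality "is continuous variables and will be analysed with repeated analysis of variance". Work ability and depression-related sick leave days, treated as ordinal, "will be analysed with mixed-effect models for ordinal data".

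The section on the CES-D outcome says: "The primary outcome is the change in depressive symptoms measured with the CES-D scale". CES-D is also the outcome that sizes the trial. Work ability is listed as primary as well (Table 1 and its own outcome section).

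On timing, Primary and secondary outcomes says: "The outcomes will be assessed utilizing the electronic survey at baseline and after 6 months". There is no intermediate visit.

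The Sample size calculation section works "with an expected dropout rate of 25" per cent and arrives at 125 participants. The Summary lists as a potential limitation that "subjects randomized to the control group might withdraw from the study", describes steps to reduce this, and gives no dropout rate by arm.

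**The concern.** The principle and the method do not fit together as written. Repeated-measures ANOVA with two time points needs both scores from each person, so the CES-D, quality-of-life and diet-quality comparisons would be made among completers and reported as intention-to-treat. Work ability and sick leave are assigned models that can retain people with baseline data only. The two kinds of primary outcome could therefore rest on different sets of people under one label.

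What is at stake is bias more than power. The sample size already allows for the loss, but randomisation protects only the comparison of everyone randomised. If the reasons for leaving differ between a counselling arm and an untreated, unblinded control arm, the completers' change scores no longer estimate the effect in the randomised population.

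**Working it through.** **1. Inputs from the article.** N = 125, allocated 1:1; dropout 25%; two measurement times; CES-D expected to fall from 14 to 9.9 in the intervention arm (14 − 9.9 = 4.1 points) with no change in controls; power 0.80; alpha 0.05. No SD, no sidedness and no dropout rate by arm are given.

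**2. The plan's own figure.** Without an SD, 125 cannot be reproduced independently, so I solved for the SD that fits. For a two-sided comparison of two means with difference 4.1 and inflation by 1/(1 − 0.25):
- SD 7.0 gives 46 per arm, 92 completers, 92/0.75 → 123.
- SD 7.03 gives 47 per arm, 94 completers, 94/0.75 → 126.

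Other readings also fit. Multiplying by 1.25 instead (100 × 1.25 = 125) implies an SD of about 7.25 to 7.3. A one-sided test implies about 7.9 to 8.0. I use 7.03 below as an assumption.

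**3. Who enters the CES-D test.** With two time points, the group-by-time interaction is a two-sample t-test on (6-month score − baseline score). No 6-month score means no change score. Lost: 125 × 0.25 = 31.25, about 31. Analysed: 125 × 0.75 = 93.75, about 94.

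**4. Power is not the main cost.** At SD 7.03, power is 80.6% with 25% loss in each arm, 79.0% with 40% control and 10% intervention loss, and 75.9% with 50% and 0%.

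**5. Bias when loss depends on baseline score.** Assume a true effect of zero, SD 7.03 at both times and baseline/6-month correlation ρ. Control loss rises with baseline CES-D (logistic, slope 1 per SD); intervention loss is random. Large-sample simulation gives the following intervention-minus-control contrast in change, where negative favours the intervention:

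| Control / intervention loss | ρ = 0.4 | ρ = 0.5 | ρ = 0.6 |
|---|---|---|---|
| 40% / 10% | −1.4 | −1.2 | −0.9 |
| 30% / 20% | −1.1 | −0.9 | −0.7 |
| 25% / 25% | −0.9 | −0.8 | −0.6 |

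This follows from regression to the mean. If the completing controls' baseline mean is shifted by s, the contrast is biased by (1 − ρ) × s. At 25%/25% loss, s is about −1.5, and (1 − 0.5) × (−1.5) = −0.75, as in the table. Unequal loss rates are not needed; different reasons for leaving are enough. Adjusting for baseline gave about 0 in every cell.

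**6. A mechanism that biases the other way.** Suppose dropouts' change is δ points worse than completers' in both arms. Each arm's completer mean is then its true mean − p × δ, so the contrast shifts by (p_control − p_intervention) × δ. With δ = 4 (assumed):
- 35% v 15%: 0.20 × 4 = 0.8, moving −4.1 to −3.3, toward no effect.
- 30% v 20%: 0.10 × 4 = 0.4.
- Equal loss: zero.

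**7. Loss that depends on the unseen 6-month score.** With the settings of step 5 at 40%/10% loss, but control loss driven by the 6-month score, the change-score contrast is biased by +0.9 to +1.4 and the baseline-adjusted or likelihood analysis by +1.5 to +2.0. Neither method is safe here, and the adjusted one is further off.

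**The case against.** The strongest reply is that the article names a principle and a test and nowhere says that non-completers are excluded. ANOVA on imputed data would be compatible with intention-to-treat, and missing-data handling is commonly left to a full protocol or statistical analysis plan, which is not shown. This stands in part. Completers-only is a consequence of the named method as written, not something the article declares, and an unseen plan could remove the conflict. But the point is not just an omission: the article fixes a particular method that, with two time points, cannot use about a quarter of those randomised, and it names a suitable class of model for other outcomes in the same paragraph.

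The size and direction of bias rest on assumed mechanisms. That stands fully: steps 5 and 6 point in opposite directions, and the article supplies no figure to choose between them.

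Four stronger readings are tempting but not supported.
- A reader might infer that withdrawal is expected mainly among controls. The Summary says only that it might happen, describes mitigation and gives no rate by arm.
- A reader might infer that the whole primary analysis is completers-only. Work ability is also primary and has a mixed-effect model.
- A reader might infer that no planned analysis would reveal the bias. The analysis plan is not shown, so this cannot be said.
- A reader might infer that the 6-month survey goes only to people who keep attending sessions. The article sets no such limit.

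**Conclusion.** The concern holds for CES-D, quality of life and diet quality. As named, the analysis uses only participants with both scores, which sits badly with an unqualified intention-to-treat statement when about 31 of 125 are expected to be lost. That count follows from the article's own figures.

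The bias is illustrative: 0.6 to 1.4 points, or roughly 15% to 34% of the planned 4.1 (0.6/4.1 and 1.4/4.1). It assumes an SD of 7.03, a correlation of 0.4 to 0.6, and loss related to baseline score in one arm only. Under other mechanisms it may be smaller, or run toward no effect. What does not depend on those inputs is that the change-score test is open to baseline-related loss, and that a baseline-adjusted or likelihood analysis removes that particular bias.

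**What to change.** For CES-D, quality of life and diet quality, replace repeated-measures ANOVA with one of the following, in the Stata already named:
- a likelihood-based mixed model on all randomised participants, with baseline and 6-month scores as responses and a common baseline mean across arms; or
- multiple imputation by arm, followed by ANCOVA of the 6-month score adjusted for baseline.

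State which is primary, and that it is the analysis meant by intention-to-treat. Because both methods are biased when loss depends on the unseen 6-month score (step 7), add a delta-adjusted sensitivity analysis in which dropouts' imputed CES-D is worsened in steps, separately by arm, for example up to the planned 4.1 points.

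The cost is a change of wording and modest programming. The main analysis would then rest on a missing-at-random assumption, which should be stated. If an existing analysis plan already provides for this, aligning the article's wording with it is enough.

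### The continuous outcomes, including the CES-D, are compared as unadjusted change over two time points; adjusting for the baseline score would give a more precise result from the same data

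*Protocol article*

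**What the plan says.** The section on statistical analyses fixes both the quantity compared and the method. The quantity is given as "The difference between groups in the change in depressive symptoms, quality of life and diet quality". The method follows in the same sentence, which says that this quantity "is continuous variables and will be analysed with repeated analysis of variance". The section on the CES-D sets the endpoint in the same form: "The primary outcome is the change in depressive symptoms measured with the CES-D scale". There are two measurement occasions: "The outcomes will be assessed utilizing the electronic survey at baseline and after 6 months". The randomisation section places allocation, 1:1, after the baseline measurements.

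No section names the baseline score, or any other covariate, as an adjustment in these comparisons. The only further step is to repeat the main analyses by gender.

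The sample size section sets the planning values: "We expect depressive symptoms to decrease in the intervention group from 14 to 9.9 points", no change in controls, 80% power, alpha 0.05, 25% dropout and 125 participants. It gives no standard deviation and no correlation between the two measurements.

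**The concern.** With two time points, repeated-measures ANOVA does use the baseline, but only by subtraction, which fixes the slope of the 6-month score on baseline at 1. The true slope is usually lower. The CES-D asks about the past week, the two measurements are 6 months apart, and the article's own limitations mention temporal variability of questionnaire answers. All of this points to a correlation well below 1.

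Two things follow. The treatment effect is estimated with more variance than the data require, in a small trial planned at 80% power with a quarter of participants expected to drop out. And if the arms differ by chance on baseline CES-D, subtraction over-corrects for that difference through regression to the mean. The gender-stratified analyses have fewer participants still, so they can least afford the loss.

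**Working it through.** **Inputs from the article.** Difference 14 − 9.9 = 4.1 points, with no change in controls; power 0.80; alpha 0.05, taken here as two-sided because sidedness is not stated; N = 125; dropout 25%. Completers: 125 × 0.75 = 93.75, or 46.9 per arm.

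**The plan's own figure.** N = 125 cannot be reproduced from the stated inputs because no SD is given, so the SD was solved for:

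- Normal approximation: SD = 4.1 / [(1.960 + 0.842) × √(2/46.875)] = 7.08.
- Forward check: SD 7.0 gives 46 per arm, and 92/0.75 = 123 in total; SD 7.05 gives 47 per arm, and 94/0.75 = 126.
- With the noncentral t, SD 7.0 and 46.9 per arm give power 0.801.

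An SD of about 7.0 is therefore implied. The article does not say whether it would be the SD of the change or of the score.

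**Step 1: the planned test is a change-score test.** With two arms and two time points, the group-by-time F equals the squared t for change scores. A simulated data set confirmed this: F = 11.851 and t² = 11.851.

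**Step 2: variance ratio.** Let σ be the SD at each time point (assumed equal) and ρ the correlation.

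- Change score: 2σ²(1 − ρ)
- ANCOVA residual: σ²(1 − ρ²)
- Ratio: (1 − ρ²) / [2(1 − ρ)] = (1 + ρ)/2

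The ratio is below 1 for every ρ below 1 and does not depend on σ. When ρ is below 0.5 the change score is also less precise than comparing 6-month scores alone, because 2(1 − ρ) then exceeds 1.

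**Step 3: power at 46.9 completers per arm for a 4.1-point difference** (noncentral t, SD 7.0; ρ is assumed throughout). Extra completers = 93.75/ratio − 93.75.

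| ρ | Ratio | Extra completers | SD 7.0 is of the change: change → ANCOVA | SD 7.0 is of the score: change → ANCOVA |
|---|---|---|---|---|
| 0.3 | 0.65 | 50 | 0.80 → 0.94 | 0.66 → 0.84 |
| 0.5 | 0.75 | 31 | 0.80 → 0.90 | 0.80 → 0.90 |
| 0.6 | 0.80 | 23 | 0.80 → 0.88 | 0.88 → 0.94 |
| 0.7 | 0.85 | 17 | 0.80 → 0.86 | 0.95 → 0.98 |
| 0.8 | 0.90 | 10 | 0.80 → 0.84 | 0.99 → 1.00 |

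**Step 4: simulation** with 47 per arm, score SD 7.1 and 4,000 replicates. Variance ratios were 0.68, 0.77 and 0.87 at ρ = 0.3, 0.5 and 0.7, slightly above the large-sample values. Power, change versus ANCOVA, was 65.5% v 82.4%, 80.2% v 89.2% and 94.7% v 97.1%.

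**Step 5: chance imbalance.** If the intervention arm starts δ points higher, the change-score estimate is expected to be off by −(1 − ρ)δ. For δ = 1 that is −0.5 points at ρ = 0.5 and −0.3 at ρ = 0.7. ANCOVA estimates the slope and so removes this shift.

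**The case against.** The strongest reply is that this is a matter of efficiency and not an error. The planned analysis answers the endpoint as defined, is unbiased under randomisation and keeps its type I error. The sample size is also framed in terms of change, so plan and sizing agree. All of that stands. The over-correction describes what happens given a particular chance imbalance; it is not bias over repeated randomisations.

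The size of the gain rests on an SD and a correlation that the article does not give. That also stands. At ρ = 0.8 the variance saving is only 10%, and the confidence interval is about 5% narrower (√0.90 = 0.95). If the implied SD belongs to the score, power at ρ = 0.7 is already 0.95 and rises by only about 2 percentage points. The relative variance saving is the same under either reading, however, and for every ρ below 1 it favours adjustment, apart from a small cost in finite samples for estimating the slope.

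It could also be said that a condensed article leaves covariates to a fuller plan. That carries little weight here, because the article names the method and the form of the comparison.

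**Conclusion.** The concern holds. The article commits the primary CES-D comparison, and those for quality of life and diet quality, to a method equivalent to an unadjusted change-score test, although baseline values measured before randomisation are available. The loss is of precision, not validity.

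Assuming equal variances at both time points and ρ of 0.5 to 0.7, baseline adjustment cuts the variance by 25% to 15%; over a wider range of 0.3 to 0.8, by 35% to 10%. The power gain depends further on which SD the 80% refers to, so the power figures are conditional illustrations. The algebra and the direction are certain; the exact gain is not. The change should be made, but the trial is not invalid without it.

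**What to change.** Replace the sentence on repeated analysis of variance. For the primary outcome, fit a linear model of 6-month CES-D on arm with baseline CES-D as a continuous covariate, and report the adjusted mean difference with its 95% CI. Use the same form for EUROHIS quality of life, the Healthy Diet Index and any nutrient intakes analysed as continuous outcomes.

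A mixed model that constrains the arms to a common baseline mean is a close alternative. With 25% dropout expected the two need not coincide, since the mixed model can also keep participants who have only a baseline score, which suits the stated intention-to-treat principle. Name one as primary.

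The cost is a sentence of analysis wording. SPSS and Stata, the programs the article names, can fit both models, and no extra data, visits or participants are needed. Make the change before outcome data are seen, so that the adjustment cannot be read as data-driven.

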Mediterranean diet interventions, utilizing either individual or group counselling, have significantly improved moderate to severe depressive symptoms (Bayes et al., 2022; Francis et al., 2019; Jacka et al., 2017; Parletta et al., 2019), with two studies demonstrating good results in cost-effectiveness analyses (Chatterton et al., 2018; Segal et al. 2020). The studies have reported a reduction in depression to mild or sub-clinical levels (Bayes et al., 2022; Francis et al., 2019; Jacka et al., 2017; Parletta et al., 2019) and an association between improved diet and reduced depression (Francis et al., 2019; Jacka et al. 2017; Parletta et al., 2019). Other intervention studies are predominantly based on secondary analyses and are heterogeneous regarding depression definition and methods (Firth et al., 2019; O’Neill et al., 2022). The MooDFOOD depression prevention study (Bot et al., 2019) using nutrition-focused behavioural therapy, multi-nutrient supplement or a combination found positive effects only among active participants and those with high baseline depressive symptoms.

To our knowledge, the effects of nutrition on depression-related work disability have not been researched before. One study found associations between dietary factors and burnout symptoms, indicating that nutrition does have a role in coping at work (Penttinen et al., 2021). Overall, lifestyle interventions have shown their potential to improve the work ability and productivity of the workforces (Grimani et al., 2019). People with a high depression risk should be a key target group for interventions to reduce work disability (Wedegaertner et al., 2013). Nutrition interventions could reduce the economic burden of depression by also preventing physical comorbidities of depression, such as obesity (Luppino et al., 2010), type 2 diabetes (Semenkovich et al., 2015) and cardiovascular diseases (Krittanawong et al., 2023).

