### Randomization

After baseline measurements and confirming that they meet the inclusion criteria, the participants will be randomly allocated in a 1:1 ratio into the intervention or control groups according to a computer-generated, blocked randomization list. A person unrelated to the study will conduct the randomization. For the participants in the intervention groups, the 6-month nutrition intervention period starts on the first day of nutritional counselling, whereas for the participants in the control group, it starts on the day randomization will be conducted. The control group will not receive any intervention but will continue their habitual diet. We will offer the control group one nutrition counselling session after the end of the intervention.

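### Gender differences in effect are to be judged from separate gender strata, which do not test whether the effect differs; no interaction is named

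*Protocol article*

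**What the plan says.** The last sentence of Statistical analyses in the protocol article reads: "The main outcomes will be examined first overall and then stratified by gender to assess potential gender differences in intervention effectiveness". It fixes a procedure (analysis within each gender) and the question that the procedure is meant to answer (whether effectiveness differs by gender).

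The same section names the models. Change in depressive symptoms "will be analysed with repeated analysis of variance"; work ability gets mixed-effect models for ordinal data. Neither description includes a gender term. Table 1 lists CES-D and two work ability indicators as primary, so the gender sentence covers at least these if main outcomes means primary outcomes.

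The sample size section addresses only the overall CES-D comparison: "We expect depressive symptoms to decrease in the intervention group from 14 to 9.9 points", and the authors "assume that depressive symptoms will not change in the control group". Power is 0.8, expected dropout 25%, alpha 0.05 and the total 125. Under Randomization, participants are "randomly allocated in a 1:1 ratio into the intervention or control groups" in blocks; stratification by gender is not mentioned. The article gives neither the expected gender mix nor an SD for CES-D.

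**The concern.** Whether an effect differs between women and men is a question about the difference of two effects. A result within women and a result within men each address another question: is there an effect in this group? Whether each reaches significance depends heavily on how many people the stratum holds. Two strata with the same true effect but different sizes, or even equal sizes at moderate power, will often fall on opposite sides of 0.05 by chance.

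The article's closing section expects the results to feed prevention programmes for this workforce. An unsupported statement that counselling helps one gender and not the other would mislead that use. With several main outcomes handled in this way, there is more than one opportunity for it.

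**Working it through.** **Inputs.** From the article: difference in change 14 − 9.9 = 4.1 points with no change in controls; N = 125; dropout 25%; alpha 0.05 (taken as two-sided); power 0.80; 1:1 allocation. Assumed: the SD of change and the gender mix, because neither is stated.

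**The plan's own figure.** Completers: 125 × 0.75 = 93.75, about 94, or 46.875 per group. Without an SD, N = 125 cannot be checked independently, but it can be solved for the SD:

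SD = 4.1 × √[46.875 / (2 × (1.96 + 0.8416)²)] = 4.1 × √(46.875 / 15.70) ≈ 7.08.

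With SD 7.09 the formula needs 47 completers per group, and 94 / 0.75 = 125.3, which agrees with 125. If dropout was instead added as N × 1.25 (100 completers), the SD is 7.32 and the results below move by no more than 1 percentage point.

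**Power within each stratum.** With two time points, the group × time test is equivalent to a t-test on change. For a stratum of n completers split 1:1, power comes from the noncentral t with n − 2 degrees of freedom and noncentrality (4.1 / 7.09) × √(n/4) = 0.578 × √(n/4). The true effect is set to 4.1 in both genders, so any apparent gender difference is false.

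P(women significant, men not) = power_w × (1 − power_m). P(discordant either way) adds power_m × (1 − power_w).

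| Women | n women / men | Power women / men | Women only significant | Discordant either way |
|---|---|---|---|---|
| 50% | 47 / 47 | 49% / 49% | 25% | 50% |
| 75% | 70.5 / 23.5 | 67% / 27% | 49% | 58% |
| 80% | 75.2 / 18.8 | 70% / 22% | 54% | 61% |
| 90% | 84.6 / 9.4 | 75% / 12% | 66% | 69% |

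Worked row, 75% women: 0.668 × 0.733 + 0.267 × 0.332 = 0.490 + 0.089 ≈ 0.58.

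**Smaller or no effect.** At half the effect (2.05 points) and SD 7.09, the even mix gives 2 × 0.161 × 0.839 = 0.27. At 90% women it is 0.259 × 0.942 + 0.058 × 0.741 = 0.29. Over SD 7.0–7.1 the range is 27–30%. With no effect in either gender, discordance is 2 × 0.05 × 0.95 = 9.5%.

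**The interaction test.** Its false-positive rate is 5% at any gender mix. Its precision is SE = SD × √(4/n_w + 4/n_m). Power for a 4.1-point difference in effect is Φ(4.1/SE − 1.96), and the difference detectable with 80% power is 2.80 × SE.

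| Women | SE | Power for 4.1 points | Detectable at 80% |
|---|---|---|---|
| 50% | 2.93 | 29% | 8.2 |
| 75% | 3.38 | 23% | 9.5 |
| 80% | 3.66 | 20% | 10.2 |
| 90% | 4.88 | 13% | 13.7 |

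**The case against.** The article does not say that two p-values will be compared. Stratum estimates with confidence intervals would fit the same sentence, and an article often leaves the formal comparison to the full protocol or SAP. This stands in part: the error rates above apply only if the strata are read by significance. But the sentence is not silent on method. It names stratification as the means of assessing gender differences, and that procedure does not by itself answer the question. An SAP that follows it inherits the gap.

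A reader might infer that the plan will usually end in a false claim that the intervention works in women and not in men. The documents do not support that. They give no gender mix and no SD. The specific pattern exceeds 50% only if women are more than about 76% of completers and the full 4.1-point effect is real. It is 25% at an even mix, about 14–25% at half the effect, and 0.025 × 0.975 = 2.4% (as a significant benefit in women only) if there is no effect at all.

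A reader might also infer that the plan neglects baseline severity, because the Introduction reports that a cited prevention trial "found positive effects only among active participants and those with high baseline depressive symptoms". That is no defect in this text. The article is silent on other subgroups, which may be left to the SAP, and the cited result names two characteristics, not one.

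Finally, the gender analysis is secondary to the overall comparison, and the interaction test itself has little power. Both are true. They limit the consequence and are the reason for an exploratory label; they do not make the strata a valid test.

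**Conclusion.** The point holds in this form: the stated method does not answer the stated question, and no interaction or between-stratum comparison is named. If significance is read stratum by stratum, a false appearance of a gender difference arises about 50% of the time at an even mix and 58–69% at 75–90% women, against 5% for an interaction test. This rests on about 94 completers, an identical 4.1-point effect in both genders and an SD of about 7. At half the effect the rate is 27–30%. Since discordance is already 50% at an even mix, the problem does not depend on one gender being scarce; the direction of the misreading does. The overall comparison is unaffected.

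**What to change.** Reword the last sentence of Statistical analyses so that any statement about a gender difference rests on an interaction, for every main outcome:

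- CES-D: the group × time × gender term in the repeated-measures model, with its estimate and 95% confidence interval. A group × gender term alone would average over baseline and 6 months and miss the difference in change.
- Both work ability indicators: the corresponding interaction in the ordinal mixed models, reported in the same way.
- Within-gender estimates with confidence intervals, shown descriptively and not used to claim a difference.
- An exploratory label, because power for a 4.1-point difference in effect is about 13–29% (50–90% women) and reaches 80% only for differences of about 8–14 points.

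The cost is a sentence or two and one added term, with its lower-order terms, per model. No new data are needed, since the planned stratification already requires gender. The downside is that the trial will rarely be able to claim a gender difference, which is a fair reflection of what a study of this size can show.
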